## Abstract

**Background:**

For many older Americans, aging in place is their preferred living arrangement. Minoritized and socioeconomically disadvantaged older adults are up to 3 times more likely to experience disability than other groups, which increases their likelihood of being unable to age in place. Bold ideas to facilitate aging in place, particularly among vulnerable populations, are needed. One such idea is the Unite care model, a community-initiated, academic-supported, cross-sector initiative that combines 2 sectors: housing and health care. The Unite care model colocates a federally qualified health center clinic on an older adult affordable housing campus in Flint, Michigan.

**Objective:**

There are two aims to this study. Aim 1 is to evaluate the implementation of the Unite care model in terms of acceptability, adoption, and penetration. Aim 2 is to determine which older adults use the care model and whether the care model promotes aging in place through risk factor reduction and improvement in the physical and social environment.

**Methods:**

We will assess the care model using a concurrent, exploratory mixed methods design. For aim 1, acceptability will be assessed through semistructured interviews with key stakeholder groups; adoption and penetration will be assessed using housing and health care records. For aim 2, residents residing in the Unite clinic building will participate in structured outcome assessments at 6 and 12 months. Risk factor reduction will be measured by change in systolic blood pressure from baseline to 12 months and change in the physical and social environment (item counts) will also be assessed from baseline to 12 months.

**Results:**

Data collection for aim 1 began in July 2021 and is anticipated to end in April 2023. Data collection for aim 2 began in June 2021 and concluded in November 2022. Data analysis for aim 1 is anticipated to begin in the summer of 2023 and analysis for aim 2 will begin in the spring of 2023.

**Conclusions:**

If successful, the Unite care model could serve as a new care model to promote aging in place among older adults living in poverty and older Black Americans. The results of this proposal will inform whether larger scale testing of this new model of care is warranted.

**International Registered Report Identifier (IRRID):**

DERR1-10.2196/47855

## Introduction

### Background

Aging in place, defined as the ability to stay in one’s current residence by securing necessary support in response to evolving needs, is overwhelmingly preferred among older adults [1-3]. Aging in place also provides health benefits for older adults [4], via sustaining established social networks and care services [5,6]. Furthermore, aging in place is overwhelmingly favored by policy makers because it may delay or avoid the costly option of institutional care; 1 year of nursing home care costs about US $80,000 [7]. For many older Americans, aging in place is their only option as assisted living facilities require significant out-of-pocket spending. Thus, strategies to support aging in place are critical, particularly among low-income Americans.

Disability is the strongest predictor of nursing home admissions [8]. Over 25% of older adults experience activity limitations and cognitive impairment [9-11]. Disability disproportionately impacts Black people and low-income Americans and negatively impacts aging in place. Minority and socioeconomically disadvantaged older adult populations are up to 3 times more likely than other groups to experience disability [12-14]. Furthermore, Black people have the highest incidence of Alzheimer disease and Alzheimer disease–related dementias (AD/ADRDs) with a 2-fold greater incidence compared with White people [15-19].

Efforts to reduce disability and optimize the environment may help facilitate aging in place. Hypertension is the most important modifiable cardiovascular risk factor [20-24] and a predictor of nursing home admission [8]. Hypertension treatment reduces the incidence of stroke [25] and may reduce the incidence of AD/ADRDs [26], which are the leading causes of disability and strongest predictors for not aging in place [27-29]. Therefore, hypertension treatment, complemented by physical and social environment optimization, may promote aging in place by reducing informal caregiving needs, unmet needs, falls, and disability [30-33].

**Figure 1 figure1:**
[figure not shown]
Unite care model.

### Aims and Objectives

This study will evaluate the Unite care model through 2 aims.

Aim 1: To assess the implementation and impact of the Unite care model in terms of acceptability, adoption, and penetration among key stakeholder groups using an exploratory mixed methods designAim 2: To determine which older adult residents who reside in the Unite clinic building use the Unite care model and whether the model promotes aging in place through cardiovascular risk factor reduction and improvement in the physical and social environment

## Methods

### Study Design

A concurrent exploratory mixed methods approach will be used to evaluate the implementation of the Unite care model.

### Ethics Approval

This study is approved by the University of Michigan Institutional Review Board (HUM00197049).

### Study Setting

Flint, Michigan is a community with a large burden of chronic disease and poverty. Flint is recovering from the water crisis, where the city’s drinking water was contaminated with excessive levels of lead for over 18 months. Flint has a population of about 80,000, 57% of which are Black; 40% live in poverty and is ranked 80 out of 83 Michigan counties on Robert Wood Johnson Foundation County Health Rankings [36].

The Unite care model takes place at a heavily charity-subsidized older adult (55 years and older) affordable apartment complex in Flint, Michigan. The apartment complex is situated within a broader, informal, older adult housing campus. Within a 3-square mile radius of the apartment complex, an estimated 700 independently living older adults reside at a public housing apartment building, a US Department of Housing and Urban Development senior living building, and single-family homes. About 75% of the older adults are Black, many earning less than US $12,000 annually.

### Aim 1: Assessing the Implementation and Impact of the Unite Care Model

#### Overview

We will determine how much and for whom (ie, adoption and penetration) and how well (ie, acceptability) the Unite care model is implemented. These implementation outcomes are necessary preconditions to understand the effectiveness of the Unite care model [37].

#### Acceptability

To measure the acceptability of the Unite care model, stakeholders from three different groups: (1) housing and health care administrators, (2) providers, and (3) older adult residents will be recruited to participate in semistructured interviews based on the theoretical framework of acceptability [38], theoretical domains framework, and Proctor’s definition of acceptability [37]. Interview guide questions will explore constructs including affective attitude, burden, perceived effectiveness, ethicality, intervention coherence, opportunity costs, and self-efficacy. Interview guides will be tailored to each population, given acceptability is distinct among those who received the care model compared to those who deliver the care model [38]. Sample interview guide questions for each group are shown in Table 1.

Housing and health care administrators (n=9) will be interviewed at the time of the clinic opening (baseline) and again at 18 months. Snowball sampling will be used to identify all key administrators. Providers (n=5) will be interviewed at 12 months and will include Unite clinic staff (nurse practitioner and medical assistant) and housing employees who provide wraparound services to residents (resident wellness director, resident service coordinator, and community health worker). Older adult residents (n=36) will also be interviewed at 12 months. Older adult positive and negative opinion leaders will be purposely sampled across three subgroups: (1) older adult residents who use the clinic (n=12), (2) older adult residents who have attempted to use the clinic (n=12), and (3) older adult residents who do not use the clinic (n=12). We will identify older adults pertaining to each subgroup based on structured survey responses (aim 2) and notes kept by the research team. Interviews will be conducted in person as possible at a location convenient to the participant, with the alternative of video or telephone calls given the individual’s availability, preference, and COVID-19 restrictions. Participants will receive US $40.

Semistructured interviews will be audio recorded, professionally transcribed, and reviewed by the research team for accuracy. We will use ATLAS.ti (ATLAS.ti Scientific Software Development GmbH), a qualitative data analysis and research software, to facilitate qualitative analysis. We will perform direct content analysis using the theoretical framework of acceptability and theoretical domains framework as a template. Two members of the research team will independently code each transcript, compare their coding, discuss discrepancies, and agree on final codes. Several strategies will be used to enhance the reliability and validity of the analysis including member checks, peer debriefing, and concurrent data collection and analysis described below.

**Table 1 table1:** Overview of aim 1 interviews.

Population	Participants, n	Timeline	Sample questions
Housing and health care administrators	9	Baseline (clinic opening) 18 months	Now, as the Unite clinic is about to open, how are you feeling about participating in this project? (affective attitude) How has the clinic impacted your daily workload? (burden and barriers)
Providers	5	12 months	How are things going at the clinic? (positive and negative affect) What do residents say about the clinic? (social norms)
Older adults	36	12 months	How do you feel about the clinic? or What do your friends think about the clinic? (positive/negative affect) What do you think would happen if you went to the clinic? (outcome expectations)

#### Adoption

Adoption, defined as the Unite care model uptake by older adult residents, will be quantified by the number of provider home visits and community health worker or resident service coordinator interactions. The number of home visits will be self-reported. Community health worker or residence service coordinator interactions will be sampled daily for 1 week per month via a Qualtrics survey completed by the community health worker. The survey will assess the number of residents served that day as well as the services provided to each resident.

#### Penetration

Penetration is defined as the proportion of people who participate in a given program. We will explore the role of clinic proximity as a predictor of Unite care model usage. The research team will obtain data from the Unite clinic electronic health record, including patient-level data (addresses, demographics, and comorbidities). Patient addresses will be geocoded using Google’s interface to identify if the patient resides on the older adult affordable housing campus and specifically in the Unite clinic building.

The primary outcome is the proportion of older adults who reside on the older adult affordable housing campus who are cared for by the Unite clinic. The research team will make 2 types of comparisons between older adults who reside in the Unite clinic building compared to older adults who reside on the campus but not in the Unite clinic building. First, for measures that can only be defined in aggregate (ie, number of new patient visits), the research team will compare mean per-patient usage measures between populations. Specifically, we will compare the mean of each usage variable divided by the number of patients living in each setting using *t* tests and the proportion of new and return visits using chi-square tests across settings. Second, for measures where individual-level data can define the population at risk (number of missed appointments and appointment timeliness), we will fit appropriate regression models to predict the usage measures (dependent variable) accounting for residence (Unite clinic building vs other older adult campus) and demographics known to predict missed appointments (age, race, and sex), comorbidities and dual eligibility (independent variables).

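### Usage by clinic proximity is divided by patients rather than residents, and no listed analysis compares the penetration proportion between the clinic building and the rest of the campus

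*Protocol article*

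**What the plan says.** All of the relevant text is in the protocol article, Methods, Aim 1, Penetration.

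- Definition: "Penetration is defined as the proportion of people who participate in a given program".
- Primary outcome: the "proportion of older adults who reside on the older adult affordable housing campus who are cared for by the Unite clinic". The base is residents.
- Question about location: "We will explore the role of clinic proximity as a predictor of Unite care model usage".
- Comparisons: two types are announced, both between the clinic building and the rest of the campus.
  - The first is "for measures that can only be defined in aggregate (ie, number of new patient visits"). For these, "the research team will compare mean per-patient usage measures between populations", by t test. The divisor is then spelled out: "we will compare the mean of each usage variable divided by the number of patients living in each setting". A chi-square test of new against return visits goes with it.
  - The second is regression of missed appointments and appointment timeliness on residence, demographics, comorbidities and dual eligibility.

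**The concern.** The section asks about reach over residents, but its comparisons by setting are made among people who have already been reached. Dividing by patients conditions on having become one. New against return visits has visits as its base. Missed and timely appointments exist only for people who have appointments. None of these shows whether residents of the clinic building are more likely to be cared for by the clinic than residents elsewhere on campus.

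The mismatch is sharpest for the one aggregate measure that the section names. New-patient visits and patients rise and fall together, so their ratio says almost nothing about uptake. A large difference in reach between the two settings could be reported as no difference in new-patient visits. Colocation is one of the model's three components (Unite Care Model section), and an advisory panel will use the results to judge whether similar models are worth developing (Overall Assessment of Unite Care Model). Reach by proximity is therefore a result that readers will look for.

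**Working it through.** The article states no expected uptake, sample size or power for this comparison, so there is no figure to reproduce. The check is algebra with an illustration.

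**Inputs**
- Residents of the clinic building: about 300 (Unite Care Model).
- Other campus residents: about 400, if the campus total of just over 700 in the Unite Care Model section includes the building (700 − 300). Up to about 700, if the 700 in Study Setting excludes it.
- New-patient visits per patient: about one. This is an assumption. It is reasonable because the clinic opens at baseline (Study Population Recruitment and Enrollment).
- Uptake: assumed throughout, as the documents give none.

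**Algebra.** Let a setting have N residents and uptake p.
- Patients = Np, and new-patient visits ≈ Np.
- New-patient visits per patient = Np / Np = 1 for any p.
- New-patient visits per resident = Np / N = p, which is penetration.

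If a share f of patients has no visit coded as new, the per-patient ratio is 1 − f. That is 0.95 for f = 5% and 0.80 for f = 20%. It still does not depend on p.

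**Illustration with 300 and 400 residents**

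| Assumed uptake | New-patient visits | Per patient | Per resident | Difference per resident (95% CI) |
|---|---|---|---|---|
| 50% vs 20% | 150 vs 80 | 1.0 vs 1.0 | 0.50 vs 0.20 | 0.30 (0.23 to 0.37) |
| 30% vs 15% | 90 vs 60 | 1.0 vs 1.0 | 0.30 vs 0.15 | 0.15 (0.09 to 0.21) |

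First row: SE = √(0.5 × 0.5/300 + 0.2 × 0.8/400) = 0.035, and 0.30 ± 1.96 × 0.035 gives 0.231 to 0.369.

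**Off-building headcount.** Keep the 80 off-building patients and let the headcount be 700. Uptake there is 80/700 = 0.114, and the difference is 0.50 − 0.114 = 0.386. With SE = √(0.25/300 + 0.114 × 0.886/700) = 0.031, the interval is 0.32 to 0.45. The headcount therefore matters more than sampling error suggests.

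**New against return visits.** With r return visits per patient, the new share of visits is 1/(1 + r). With r = 2 in both settings it is 0.33 against 0.33, whatever the uptake. With r = 3 against 1 it is 0.25 against 0.50, which reflects return use and not reach.

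**Could the data answer the question?** At an assumed two-sided 5% level, a per-resident comparison of 20% against 10% has power of about 0.96 with 400 other residents and 0.98 with 700.

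**The case against.** The strongest reply is that patients is a slip for residents. The section separates aggregate-only measures from those where individual data define the population at risk. Clinic patients have individual records with geocoded addresses, so there would be little reason to call new-patient visits aggregate-only unless the population at risk were all residents, many of whom have no record. On that reading the ratio approximates penetration by setting. This is plausible and may be what was intended. But the section says per-patient and then names patients as the divisor, and elsewhere it uses patient for people in the clinic record and older adults who reside for residents. An analyst following the text would use the wrong divisor.

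A second reply is that intensity of use is a proper part of usage, the word in the proximity question, and that the work is exploratory. That stands. It justifies keeping the per-patient measures, but it does not supply the missing contrast in reach.

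A third is that a condensed article may leave detail to the full protocol. That does not remove the point, because the article itself fixes the divisor and lists the comparisons.

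Three stronger readings are tempting, and the text does not support them:
- A reader might infer that the t test has no variance to work with. That holds only if each measure is a single total per setting. The article does not fix the unit of observation, and repeated period totals would supply variance.
- A reader might infer that the planned analyses can show no proximity effect at all. Per-patient counts other than new-patient visits can differ by setting; they measure intensity.
- A reader might infer that the primary penetration result is wrong. The campus-wide proportion has the right base.

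**Conclusion.** The point holds on the literal wording. The comparisons by setting use patients, visits or appointments as their base, while penetration is defined over residents, and no listed analysis contrasts the penetration proportion between the clinic building and other campus housing. For new-patient visits the planned ratio carries no information on uptake, provided each patient has about one such visit, or the share without one is similar in the two settings. The documents do not say how patients already known to the health center are coded.

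The effect is confined to the proximity question in Aim 1. The Aim 2 blood pressure analysis does not depend on it. The uptake figures are illustrative and show only how far the two divisors can diverge. If residents were meant, the fault is one of wording, but it still prescribes the wrong divisor and should be corrected.

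**What to change.** 1. Replace the number of patients, as divisor, with the number of older adults residing in each setting.
2. Add the penetration proportion by setting, clinic building against other campus housing, as a difference in proportions with a 95% CI.
3. Compare new-patient and total visits as counts per resident with a rate ratio, using the resident number as offset. For total visits, use a variance that allows for several visits by one person.
4. Keep the per-patient measures, new against return visits, and the appointment regressions, labelled as describing use among people in care.

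The cost is a few sentences in the plan. Geocoded addresses already give the numerators by setting, and the campus-wide primary proportion already needs a headcount; the building count is stated. The downside is that the off-building headcount is an estimate, so items 2 and 3 should be reported over the range from about 400 to 700 unless a firmer count is obtained.

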#### Integration of Qualitative and Quantitative

The qualitative (acceptability) and quantitative data (adoption and penetration) will be collected and analyzed during the same time. Integration will merge the qualitative and quantitative data after their respective analyses are complete [39]. We will merge the data through narrative integration, whereby the qualitative results are presented followed by the quantitative results and jointly displayed in a table. Conceptually, the research team believes that the Unite care model must be found to be acceptable by stakeholders as a precursor to adoption and penetration. Thus, the qualitative data will be presented first. The research team will also assess the concordance of the data integration. If discordance is identified, additional data may be gathered.

### Aim 2: Determining Which Older Adults Residing in the Unite Clinic Building Use the Unite Care Model and Whether the Model Promotes Aging in Place

#### Overview

We seek to understand the usage of the Unite care model and to assess the impact of the components of the person-environment fit model, hypertension as a predictor of disability, and the environment. This is a prospective observational study with baseline, during, and post-Unite care model initiation assessments.

### Study Population Recruitment and Enrollment

Residents of the Unite clinic building (n=300) will be recruited to complete in person, prospective observational assessments in which they will be asked structured interview questions and have their blood pressure taken. Residents will be recruited from building central locations, including community and recreation rooms, in addition to fliers, word-of-mouth, and door-to-door knocking. Recruitment will continue until all residents have been contacted and provided the opportunity to consent or decline. The housing staff will aid the research team in contacting hard-to-reach residents. Residents who do not respond to the research team and housing staff after multiple contact attempts will be considered a decline. We will use our ongoing successful retention strategies, which include maintenance of contact and obtaining alternate contact information, including those of family members, in the event of change in contact information. The assessments will take place in a private space in the Unite clinic building. Participants will be given US $20 at baseline and US $25 for each outcome assessment.

Baseline assessments will begin at the time of the Unite clinic opening, with 6- and 12-month outcome assessments. The assessments will measure resident cognition, activity limitations [40-42], blood pressure, Unite clinic usage, physical [43] and social environment [44], health-related social needs [45], and housing transition information. Blood pressure will be measured by research staff using the OMRON 7 series upper arm blood pressure monitor (OMRON Healthcare, Inc) in accordance with national standards for measurement. Housing status transition will be obtained from the Unite clinic building records including 2 years prior to the start of the Unite care model. Participant responses and blood pressure measurements will be stored in a Research Electronic Data Capture database (Vanderbilt University). Table 2 depicts which measures are assessed at each outcome assessment.

**Table 2 table2:** Comparison of aim 2 measures by outcome assessment.

	Baseline	6 months	12 months
Sociodemographics	✓		
Comorbidities	✓		
Self-rated health	✓		✓
Activity limitations	✓		
Cognitive impairment	✓		
Unite care model usage		✓	✓
Blood pressure measurement	✓	✓	✓
Physical environment	✓		✓
Social environment	✓		✓
Housing status	✓	✓	✓

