### Data Analysis

The primary analysis is the change in systolic blood pressure (SBP) from baseline to 12 months. Meta-analyses have found that for a given blood pressure, SBP predicted over 90% of the risk of ischemic heart disease and stroke and that a 2 mm Hg decrease in SBP could reduce stroke and ischemic heart disease mortality [46]. Analysis will fit a linear regression model with the outcome of 12-month SBP, including baseline SBP and a binary predictor of Unite care model patient (yes vs no) as independent variables.

Other secondary analysis end points will include determining whether functional and cognitive limitations are associated with care model usage, change in physical and social environment, and moves out of the Unite clinic building. To determine if functional and cognitive limitations, including activity limitations and AD/ADRD are associated with Unite care model usage, the research team will build a logistic regression model predicting Unite utilization, including age, sex, race, ethnicity, AD/ADRD status, level of functional disability, self-reported health, and baseline hypertension as independent variables. Change in physical and social environment (item counts) will be assessed using a Poisson regression with an outcome of 12-month values, adjusting for baseline values and including an intervention indicator. Moves out of the clinic building will be assessed by comparing moves out of the building in the 2 years prior to the Unite care model compared to year 2 of the Unite care model.

Of the 300 older adults residing in the Unite building, we estimate that 5% will elect not to enroll, resulting in a study population of 285 older adults. We estimate that we will have 89% power to detect a 2-point change in SBP within older adults assuming a mean baseline SBP of 162 mm Hg and SE of change in SBP over time of 10 mm Hg, based on prior data in this community and community studies [47,48], and a 10% loss to follow-up using an analogous test to our primary analysis. If loss to follow-up increases to 20%, power to detect a 2-point change in SBP would decrease to 85%. The effect may be larger. We will have 100% power to detect a 4-point SBP change if loss to follow-up were 20%.

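### Unite use in aim 2 is measured, as far as stated, only by interview at 6 and 12 months, so use before the baseline SBP and recall error would go undetected

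*Protocol article*

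**What the plan says.** All references are to the protocol article.

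- **How use is measured (Study Population Recruitment and Enrollment).** Residents attend in-person assessments in which "they will be asked structured interview questions and have their blood pressure taken". On content: "The assessments will measure resident cognition, activity limitations [40-42], blood pressure, Unite clinic usage". In Table 2 the row "Unite care model usage" is ticked at 6 and 12 months and blank at baseline. For housing transitions the same section names building records as the source. It names no record source for use.
- **User status elsewhere (Acceptability).** Residents are sorted into users, attempted users and non-users for the aim 1 interviews from aim 2 survey answers and research team notes.
- **Timing (Study Population Recruitment and Enrollment).** "Baseline assessments will begin at the time of the Unite clinic opening, with 6- and 12-month outcome assessments". Recruitment goes on until every resident has been contacted. The Results section dates the aim 2 interviews from June 2021 to November 2022.
- **Where use enters the analysis (Data Analysis).** The primary model regresses 12-month SBP, "including baseline SBP and a binary predictor of Unite care model patient (yes vs no) as independent variables". The environment models carry an intervention indicator. A logistic model takes use as its outcome, with dementia status and functional disability among its predictors.
- **Clinic records (Penetration, aim 1).** "The research team will obtain data from the Unite clinic electronic health record, including patient-level data". The same section analyses missed appointments and appointment timeliness. Nothing ties these data to aim 2.

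**The concern.** User status is the exposure in the primary model and the outcome in the usage model. If the interview is its source, two weaknesses follow.

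First, a resident enrolled some weeks after opening may already have been seen at the clinic. Part of any benefit is then in the baseline SBP that the model adjusts for. With no usage item at baseline, the aim 2 data as described cannot identify such residents.

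Second, recall may be poorer among residents with cognitive impairment, and cognition is one of the predictors whose association with use is to be tested. Reporting error that varies with cognition would enter that association directly. It could also bias the SBP contrast.

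At stake are the user versus non-user SBP difference and the answer to who uses the model. The study obtains clinic data that could address both weaknesses.

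**Working it through.** **Stated figure.** No figure in the article quantifies exposure error. The nearest is the 89% power for a 2 mm Hg SBP change. It reproduces as a one-sample test of change (two-sided 5% level assumed, the stated 10 mm Hg taken as a standard deviation): n = 285 × 0.90 = 256.5, and Φ(2/(10/√256.5) − 1.96) = Φ(1.24) = 89.3%. The calculation has no exposure term, so it neither supports nor refutes this point.

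**Step 1: can baseline follow a first visit?** June 2021 to November 2022 is about 17 months. Less 12 months of follow-up, this leaves 17 − 12 = 5 months. If interviews started at opening and the last 12-month visits were on time, baselines ran to about November 2021 at the latest. Late final visits would shorten the span. The article gives no count of residents seen before baseline.

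**Step 2: what would use before baseline do?** Let f be the share of users already exposed at baseline, g the share of their effect already present in baseline SBP, and treat the coefficient of baseline SBP as 1. Then

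observed difference = true difference × (1 − f × g).

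For a true 2.0 mm Hg, with f and g assumed:

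| f | g = 0.5 | g = 1 |
|---|---|---|
| 10% | 1.9 | 1.8 |
| 25% | 1.75 | 1.5 |
| 50% | 1.5 | 1.0 |

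In the planned regression the loss is f × g times the fitted baseline coefficient, so a coefficient below 1 gives a smaller loss than the table shows.

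**Step 3: what would recall error do?** For nondifferential error,

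observed difference = true difference × (PPV + NPV − 1).

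With an assumed 50% users:

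- Sensitivity 0.85, specificity 0.95: PPV = 0.425/0.45 = 0.944, NPV = 0.475/0.55 = 0.864, factor 0.808. A 2.0 mm Hg difference appears as 1.6.
- Sensitivity 0.80, specificity 0.90: PPV = 0.40/0.45 = 0.889, NPV = 0.45/0.55 = 0.818, factor 0.707. A 2.0 mm Hg difference appears as 1.4.

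Over user shares of 20% to 50%, sensitivity 0.7-0.9 and specificity 0.90-0.95, the observed value runs from 1.12 to 1.70 mm Hg.

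**Step 4: limit of step 3.** The formula requires error unrelated to the outcome. If recall depends on cognition, and cognition is related to SBP, the bias can go either way. In the usage model, under-reporting by impaired residents would hide use in that group and over-reporting would create it.

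**The case against.** The Data Analysis section names no source for the SBP predictor. Being a clinic patient could be read from the clinic record, and an article commonly leaves the source, threshold and window of such a variable to the full protocol or analysis plan. A blank usage cell at baseline is also natural for residents enrolled as the clinic opened. These arguments stand in part: that the interview feeds the primary model is an inference, and a missing threshold or window would not by itself be a finding. They do not remove the point. The interview is the only aim 2 measure of use that the article states, the Acceptability section also relies on it, and Table 2 fixes its timing.

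A reader might infer several stronger things that the documents do not support:

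- **That use is in fact misclassified, or that treatment did precede baseline.** No error rate and no count of early users is given.
- **That the SBP effect is necessarily shrunk.** This holds only under nondifferential error, whereas error linked to cognition has no assured direction.
- **That the 179 − 149 = 30 residents without a 6-month assessment weaken the SBP and environment models.** Those models need 12-month values, and use is asked again at that visit. Only the usage model could be affected.
- **That "The number of home visits will be self-reported" shows the aim 2 exposure to be self-reported.** That sentence concerns aim 1 adoption and does not say who reports. Its tension with the abstract's "adoption and penetration will be assessed using housing and health care records" is a separate wording matter.
- **That dated visit records are already in hand.** The fields listed are addresses, demographics and comorbidities. Visit dates are only implied by the appointment measures.

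**Conclusion.** The point holds as a risk that the plan as written cannot detect. The only stated aim 2 measure of use is an interview item at 6 and 12 months. Baselines could follow opening by up to about 5 months, assuming interviews began at opening and 12-month visits were on time. Cognition may affect recall and is itself a tested predictor of use.

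The size and direction of any bias cannot be known from the documents. The fall from 2.0 to about 1.4-1.6 mm Hg is an illustration that rests on assumed sensitivity and specificity, 50% users and nondifferential error. It is not an estimate for this study. Aim 2 analysis is scheduled for spring 2023, after data collection ended, and the repair needs no further resident contact for data. It should be made before analysis, but the documents do not show that the primary comparison is invalid.

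**What to change.** 1. For consented aim 2 participants, link to the Unite electronic health record already being obtained for aim 1. Derive or verify the yes/no user variable from visit dates relative to each resident's baseline date. Fix its source, threshold and window in writing before analysis.
2. Flag residents with a visit before their baseline SBP and repeat the SBP model without them.
3. Keep self-report, together with community health worker contact, as a sensitivity definition. A record-only definition could class residents whose only contact was with that worker as non-users, because nothing shows that those contacts are in the clinic record. The Adoption survey samples them only one week per month.
4. Use a 6-month cut-off for becoming a user only as a sensitivity analysis. As the main definition it would count care begun after month 6 as none.

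**Cost.** Linkage for at most the 179 enrolled residents, 131 of whom have the 12-month outcome; possibly an ethics or authorization modification; and confirmation that the record extract holds visit dates. If it does not, the extract must be extended before steps 1 and 2 can be done.
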